| Objectives:  **Primary objectives:** The study aims to **verify the equivalence of clinical outcomes** of endoscopic surgery to those of a conventional surgical technique for patients with lumbar spinal stenosis. In addition, the prospective clinical data of endoscopic surgeries will be analyzed to establish the **basis for clinical practice guidelines** and present a guideline for selection of treatment methods in clinical practice.  **Secondary objectives:** To this end, the **clinical efficacy and safety** of posterior decompressive laminectomy using the full-endoscopic uniportal technique will be compared with those of the conventional surgical method in patients with lumbar spinal stenosis at three study sites. | | | |
| **Rationale:**  According to the Health Insurance Review and Assessment Service (HIRA), the number of patients with spinal diseases, the target population of this study, was reported to be around 3.63 million in 2018 alone, showing an increase of 450,000 patients over the past five years. In particular, the number of patients with lumbar spinal stenosis (LSS) increased by approximately 32.4% in 5 years. According to the 2018 Statistical Yearbook of Surgery by the National Health Insurance, there were 7,218 cases of endoscopic spine surgery, an increase of 41.3% from 5,108 cases in the previous year, and the treatment cost also increased by 45.9%. Compared to the increase of 2.4% in the number of conventional spine surgeries from 165,573 cases to 169,706 cases for the same period, a significant increase is confirmed, indicating that the cases of endoscopic spine surgery show a trend of remarkable growth. In addition, the prevalence of spinal diseases is expected to gradually escalate with the increase in the senior population, and the burden of increased medical expenses for the treatment is also projected.  Posterior decompression in lumbar spinal stenosis and posterior lumbar discectomy in lumbar disc herniation are the most conventional methods used to resolve the patient's symptoms. | | | |

The conventional methods have problems in terms of much bleeding, postoperative pain, instability and a decrease of muscles around the spine, and therefore, minimally invasive surgery is performed to preserve anatomical structures. Unilateral laminectomy bilateral decompression (ULBD) is the representative, most commonly used minimally invasive technique, and other methods such as spinous process osteotomy and endoscopy are also used.

It has been reported that minimally invasive surgery has a number of advantages compared to the conventional surgical technique, and the clinical outcomes are not different from those of the conventional open laminectomy. Recently, surgical techniques of spinal decompression and discectomy using endoscopy have been developed and applied in clinical practice. The endoscopic spine surgery is classified into uniportal endoscopic technique and biportal endoscopic technique depending on the number of ports for insertion of instruments. Since the surgical site is accessed through a skin incision of less than 1 cm, damage to the normal structure can be minimized, resulting in fewer postoperative complications such as pain and epidural adhesion.

However, although spinal surgeries **have been reported with good clinical outcomes in retrospective studies, clinical outcomes have not been confirmed in a multicenter, prospective, randomized clinical trial**. In addition, while the conventional open laminectomy and microscopic surgery currently performed on patients with lumbar spinal stenosis are covered by national health insurance and are appropriately applied for patients in need of surgical treatments, endoscopic spine surgeries are not fully accepted for health insurance coverage, and are performed only for limited number of patients with lumbar disc herniation. Most of the endoscopic sinal surgery studies reported in Korea are retrospective studies, and **only a handful of level 1 studies are available for establishing the efficacy and safety** of the endoscopic surgery compared to the conventional open laminectomy. Therefore, in this study, the efficacy and safety of endoscopic surgeries were compared with those of conventional open laminectomy with established clinical outcomes through a multicenter, prospective randomized trial.

Study design:

- Conduct a prospective, randomized study as a multicenter, assessor-blind, randomized, controlled, prospective clinical trial.
- The study will be conducted with the endoscopic group (Group 1) and conventional surgery group (Group 2) depending on the patient group assigned to the sub-study.

- In addition to the difference in surgical method, the two groups will be compared by recording the variables for radiology and clinical surgical outcomes while receiving the identical treatments and follow-up (day of surgery as well as 2 weeks, 3 months, 6 months and 1 year after the surgery). The patients planned to be enrolled in this study will be given an explanation on the objectives and method of the study from the study coordinators before participating, and become enrolled in the study by signing the informed consent form. Screening assignment numbers are assigned as a 6-digit number – the first digit of the randomization number represents the clinical trial site; the second digit represents the sub-study; the third digit represents S in Screening; and the last three digits represent the serial number for enrollment (e.g. B1S-001 -> first screened patient for detailed surgery 1 at Seoul National University Bundang Hospital)

- Among subjects who have agreed to participate in the study voluntarily and have signed the informed consent form, those who meet the inclusion and the exclusion criteria will be randomized to one of the two groups in 1:1 ratio.
- For randomization, the permuted block randomization method will be used. Randomization will be applied to subjects in sequential order starting from Subject no. 1 using iCReaT, a web-based eCRF. The investigator will perform the corresponding surgery depending on the randomization result for each subject. To minimize bias, randomization will be performed by a researcher and the randomization code will be notified to the surgeon immediately prior to the surgery.
- The randomization number is assigned as a series of 5-digit number in which the first digit represents the clinical trial site; the second digit represents the sub-study; and the remaining 3 digits represent the serial number for enrollment (e.g. B1-001 -> first enrolled patient for detailed surgery 1 at Seoul National University Bundang Hospital)
- All basic tests and questionnaires will be conducted at prior to surgery, on the day of surgery as well as at follow-up 2 weeks, 3 months, 6 months and 1 year after the surgery.

Before surgery, conduct pre-surgery radiological assessment, clinical physical examination (age, gender) and medical history taking (disease history, surgical history) for these subjects, and check the results of the clinical laboratory tests (CBC, Routine chemistry). Check for complications based on radiological imaging tests (X-ray) before surgery, immediately after surgery (X-ray, MRI or CT), and 2 weeks, 3 months, 6 months and 12 months after the surgery. Perform clinical assessments by conducting questionnaires on VAS, ODI, EQ5D, gait, satisfaction, and POSAS before surgery and 2 weeks, 3 months, 6 months and 12 months after the surgery. Immdiately after the surgery, take measurements on the items related to the surgery (postsurgery bleeding, duration of surgery, hospital stay, Creatine Kinase (CK, CPK) at postoperative day 1) to compare surgery-related items.

- However, if the subject is unable to visit the site at planned dates due to unavoidable reasons (such as safety issues due to COVID-19), non-face-to-face treatment or telephone surveys permitted by the current laws can replace the actual outpatient visit.

Eligibility:

Patients with ≥ grade B lumbar central canal stenosis who agree to undergo one to two segment posterior spinal decompression surgery, those who can be followed up for at least 1 year.

Inclusion Criteria:

1. Ages 20 to 80
2. Patients ≥ grade B lumbar central canal stenosis who agree to undergo one to two segment posterior spinal decompression surgery
3. Those who can be followed up for at least 1 year
4. Subjects who signed the informed consent form on own (if the subject is able) or through a legally authorized representative after fully understanding the details of the clinical trial

Exclusion Criteria:

1. Patients with spondylolisthesis (Meyer grade ≥ II)
2. Those who have had the same segmental surgery
3. Degenerative lumbar scoliosis (Cobb angle > 20°)
4. Cause of the lumbar spinal stenosis is not of degenerative nature or it is caused by lumbar disc herniation
5. Presence of other spinal disorders in the lesions of the lumbar spinal stenosis (e.g. ankylosing spondylitis, spinal tumor, spinal fracture)
6. Psychological disorders (such as dementia, intellectual disability, or drug abuse)
7. Those who have refused to participate in the study
8. Other patients deemed ineligible by the investigator to participate in the clinical trial

Treatment Plan:

- Surgical Method

1. Interlaminar full-endoscopic decompressive laminectomy

As shown in the figure below, decompressive laminectomy is performed using endoscopic instruments and instruments for spinal surgery. The method can minimize the injury to normal tissue. After making a skin incision of about 1 cm, the endoscope is introduced, the location is checked on the X-ray, and the radiofrequency electrode is applied to control bleeding. After exposing the lamina, a direction-variable drill for endoscopy is used to perform laminectomy while minimizing the injury of the facet joint to expose the ligamentum flavum. During the process of ligamentum flavum detachment, the inferior edge of cranial lamina and superior margin of the caudal lamina are carefully removed if necessary for additional decompression and to secure operation field for improved visualization.

[figure not shown]

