# Patients with lumbar spinal stenosis who will undergo uniportal endoscopic decompressive laminectomy

- Target sample size: 120 subjects (Study group: 60 subjects, Control group: 60 subjects, including 20 % drop-out rate)
- Primary outcome: ODI (Oswestry disability index)
- According to a previous study [1], the MCID (Minimal clinical important difference) of ODI was 12.8 and in another previous study [3], the standard deviation of the ODI value at 1 year after decompressive laminectomy was 18.8. Assuming an equivalence limit of 12.8, under the conditions of alpha = 0.05, power = 0.90, two-sided 95% confidence interval, and follow-up loss at 20%, 60 participants are needed in each group.

[figure not shown]

Subject Recruitment Plan

This is a prospective, multicenter study which will recruit subjects at the Department of Neurosurgery of Seoul St. Mary’s Hospital, Chundam Woorideul Spine Hospital and the Wiltse Memorial Hospital (Anyang). Those who are planning to undergo one-segment or two-segment decompression surgery for lumbar spinal stenosis will be recruited as subjects and advertisement for subject recruitment will not be used.

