Statistical analysis method: Equivalency will be declared if the upper and lower limits of the 95% confidence interval (CI) of the treatment difference value of each group’s ODI score at 12 months postoperatively fall within the pre-defined equivalence margin (+-12.8).

1. Secondary Endpoints

The secondary endpoints for this trial include clinical outcomes (VAS, EQ5D-5L, ODI, walking distance and time, satisfaction after surgery, time required to return to daily activities postoperatively, POSAS), radiographic outcomes, and other surgery-related outcomes.

Statistical analysis method: For each group, the differences from the baseline values to the postoperative values and differences in the pattern of change between the two groups are analyzed using repeated measures analysis of variance (ANOVA). In addition, for specific within-group or between-group comparisons at each time point, the t-test is used, while applying the adjusted significance level considering the multiplicity of the test.

Satisfaction after surgery, time required to return to daily activities postoperatively, Patient and Observer Scar Assessment Scale(POSAS scale)

Statistical analysis method: The satisfaction after surgery, the time to return to daily activities postoperatively, and POSAS scale score at the time of final postoperative follow-up are comparatively analyzed between the two groups using the t-test.

- Radiographic outcomes

Examination of the occurrence of complications during the final follow-up using simple radiographs (Development of spondylolisthesis, progression of degenerative lumbar spinal conditions, etc.), analysis of surgical outcomes through postoperative MRI (or CT)

- Statistical analysis method: The occurrence of complications is examined for each group, and Chi- square test or t-test is used for comparative analysis on the difference between the two groups for the degree of central canal release and the canal dimension measured using postoperative MRI or CT.

- Other surgery-related outcomes

Comparison between the two groups on other surgery-related outcomes. [size of the surgical skin incision, postoperative drainage, operative time, duration of hospitalization (hours), Postoperative (From immediately after surgery to discharge from the hospital), postoperative Day 1 creatine kinase (CK, CPK)]

Statistical analysis method: The degree of difference between the two groups is evaluated using the chi-square test or t-test.

General Statistical Analysis

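### Operative outcomes mix one- and two-segment surgery but are compared by unadjusted tests, which costs precision and leaves them open to chance imbalance in segments

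*Protocol*

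**What the plan says.** Two places in the Protocol admit both extents of surgery. Inclusion Criteria, item 2, accepts "Patients ≥ grade B lumbar central canal stenosis who agree to undergo one to two segment posterior spinal decompression surgery". The Subject Recruitment Plan repeats it: "Those who are planning to undergo one-segment or two-segment decompression surgery for lumbar spinal stenosis will be recruited as subjects". Neither gives a quota or an expected share. The secondary objective places the trial "in patients with lumbar spinal stenosis at three study sites".

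On allocation, Study design states that eligible subjects "will be randomized to one of the two groups in 1:1 ratio" and that "For randomization, the permuted block randomization method will be used". Setting the control group and randomization method says the same. Neither names a stratification factor. The randomisation number is built so that "the first digit represents the clinical trial site; the second digit represents the sub-study; and the remaining 3 digits represent the serial number for enrollment"; it carries no code for segments.

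On data, the list of observation items and the Schedule of Activities do not include the number of segments.

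On analysis, the Secondary Endpoints part on other surgery-related outcomes covers incision size, drainage, operative time, hospital stay and Day 1 CK, and states: "The degree of difference between the two groups is evaluated using the chi-square test or t-test". No analysis in the Protocol names segments or site as a covariate.

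**The concern.** A second operated level is extra surgical work in either arm. It can plausibly lengthen the operation and raise drainage, CK and stay, although the Protocol gives no figure for this. Whether one or two segments are planned is part of eligibility, so it is known before randomisation. Permuted blocks balance the number of patients per arm, not the number of two-segment patients per arm.

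The primary analysis tests equivalence on ODI and is not built to show that either technique is better. The Rationale's case against conventional surgery cites bleeding and loss of muscle around the spine, and drainage and CK are the outcomes closest to those claims. If the arms happen to differ in two-segment cases, part of any observed difference in these outcomes may come from the number of levels operated. Even with balanced arms, the spread between one- and two-segment patients stays in the error term and widens the interval.

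**Working it through.** **The plan's own figure.** The only planned number used here is 60 per group. From Statistical Consideration: margin 12.8, SD 18.8, power 0.90, alpha 0.05, 20% loss. Two one-sided tests at 5% each give n = 2 × (18.8 × (1.645 + 1.645) / 12.8)² = 46.7, so 47, or 59 after dividing by 0.8. The exact t version gives 48, and 48 / 0.8 = 60. The figure is reproduced. (It corresponds to a 90% interval, not the stated 95% one; that is a separate matter.) Operative outcomes are collected around surgery, so 60 per arm is used below.

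**Assumed inputs.** The Protocol gives neither the two-segment share p nor the effect d of a second segment in within-stratum SD units. I take p = 40% (20% to 50% as a range) and d = 0.5 to 1.5.

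**Chance imbalance.** The SD of the arm difference in two-segment share is √(2p(1−p)/60):
- p = 0.2: √(2 × 0.16/60) = 0.073
- p = 0.4: √(2 × 0.24/60) = 0.089

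Exact hypergeometric figures for p from 20% to 50%: an imbalance of at least 10 percentage points has a 25% to 36% chance, and of at least 15 points a 4% to 10% chance.

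**Standard errors and interval width at p = 0.4.** Unadjusted SE = √(2(1 + 0.24d²)/60). Adjusted SE = √(2/60) = 0.183. CI ratio = 1/√(1 + 0.24d²). Typical shift (one SD of imbalance) = 0.089 × d.

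| d | Unadjusted SE | CI ratio | Narrowing | Typical shift | Shift / unadjusted SE |
|---|---|---|---|---|---|
| 0.5 | 0.188 | 0.97 | 3% | 0.045 | 24% |
| 1.0 | 0.203 | 0.90 | 10% | 0.089 | 44% |
| 1.5 | 0.227 | 0.81 | 19% | 0.134 | 59% |

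At p = 0.2 and d = 1 the shift is 0.073 against √(2 × 1.16/60) = 0.197, or 37%.

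The unadjusted SE already contains this variation. At d = 1, 0.183² + 0.089² = 0.0333 + 0.0080 = 0.0413 = 0.203².

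**Type I error of the unadjusted t-test** (40,000 simulated trials per setting, 60 per arm):
- Overall: about 5.0% in every setting.
- d = 1, p = 30% or 50%: about 8% given an imbalance of at least 10 points, about 12% given at least 15 points, and 3% to 4% when it is below 10 points.
- d = 2, p = 50%: 12%, 26% and 1% respectively.

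**The case against.** The strongest reply is that nothing here is invalid. After 1:1 randomisation an unadjusted t-test is unbiased on average and holds its level. Covariates and list specifications are also often left to a statistical analysis plan, which is not at hand. Much of this stands. Silence on stratification does not prove that none exists, and a randomisation number coded by site is compatible with separate site lists, though the text does not say so. What remains is that the Protocol itself names the unadjusted tests for these outcomes and does not list the covariate that a better analysis would need.

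Three stronger readings are tempting and not supported.

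- A reader might infer that imbalance will distort the operative results. It is possible, not certain, and the overall error rate is unaffected.
- A reader might infer that the shift is as large as the standard error, by setting 1.96 × 0.089 = 0.175 SD beside 0.183 SD. That compares a 95% extreme with the SE of the adjusted analysis. Like for like, at 40% and 1 SD, it is 0.089 against 0.203.
- A reader might infer that the ODI equivalence conclusion is at risk. Nothing in the Protocol shows that segments matter for 12-month ODI to a degree that would threaten it.

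Incision size is a weak example. The techniques differ by design, about 1 cm against about 3 cm, so chance imbalance is an unlikely explanation of a difference there.

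**Conclusion.** The point holds as a cheap improvement to the secondary operative outcomes: operative time, drainage, CK and hospital stay. The planned tests are valid on average but less precise than they need be, and their result in a given sample may be shifted if two-segment cases fall unevenly.

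The gain is modest at 0.5 SD and worthwhile from about 1 SD. At 1 SD and 40%, the unadjusted test needs 1.24 times the patients for the same precision. These sizes rest wholly on an assumed share and effect, and on allocation that does not already balance segments. The value of a site term was not quantified; it is included because numbers are issued by site.

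**What to change.** - Add one CRF field, completed before randomisation: planned number of segments (1 or 2). Use the planned number, since the number actually operated is determined after allocation.
- In the Secondary Endpoints text on other surgery-related outcomes, replace the plain t-test for continuous outcomes with a linear model with terms for arm, planned number of segments and site. Report the adjusted arm difference with its 95% confidence interval.
- Keep the chi-square or Fisher test where binary events are sparse. A logistic model with segments and three sites could be unstable there, and it estimates a conditional odds ratio.
- Optional, if enrolment is still open: stratify the remaining allocation by planned segments. This adds a few incomplete blocks and is not needed for the gain above.

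The cost is one field and slightly more analysis work. The model has five parameters instead of two, leaving 115 rather than 118 residual degrees of freedom with 120 patients. No extra patients are needed, and the primary analysis does not change.

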**2) Conventional open decompressive laminectomy**

This method is the commonly applied technique of laminectomy in which a midline incision is made and the bilateral hypertrophied ligamentum flavum is removed with open bilateral access. After disinfection of the surgical site, the surgical site is located with a simple radiograph of the lateral view for the lumbar spine. A skin incision is performed at a length of about 3 cm from the midline of the surgical site to the long axis, and this is sufficient to secure the operational field. After detaching the paraspinal muscles from the spinous process, lamina, and vertebral joint, the fascial flap is opened and the operational field is secured using a retractor.

In the intervertebral foramen, the proximal ligamentum flavum is clearly visible in the transverse process of the upper vertebrae and the distal face of the pedicle. The ligamentum flavum detachment of the target area is carefully performed not to injure the nerve root running below the distal end of the transverse process of the upper vertebrae. During ligamentum flavum detachment, the inferior edge of the cranial lamina and the superior margin of the caudal lamina are carefully removed for additional decompression and securing the operational field. At this time, care must be taken not to damage the facet joint. Thereafter, the nerve root is viewed and decompression is performed by checking the nerve running to the proximal part of the pedicle of the lower vertebrae for sufficient decompression along the nerve root to the distal end. After decompression is performed on the contralateral side in the same way, it is checked whether the bilateral running of the nerve root is without restriction. Then, hemostasis is performed at the surgical site, the surgical site is sutured and disinfected to complete the surgery.

[figure not shown]

Setting the control group and randomization method

This study will be conducted by dividing the patients with lumbar spinal stenosis who will undergo posterior spinal decompression surgery into the interlaminar full-endoscopic laminectomy group (group 1) and conventional surgery group (group 2) through a prospective, randomized trial. Interlaminar full-endoscopic laminectomy is currently the preferred minimally invasive surgery method. Unilateral laminectomy bilateral decompression (ULBD) is a minimally invasive surgical method without endoscopy, and the clinical outcomes have been reported to show no significant difference from those of conventional surgical techniques. Therefore, it is necessary to verify the equivalence in clinical outcomes between the interlaminar full-endoscopic laminectomy and the conventional open decompressive laminectomy.

This is a prospective study, and among the subjects who voluntarily gave their consent to participate in the study and signed the ICF, those who are eligible according to the inclusion and exclusion criteria will be randomized to one of the two groups at a ratio of 1:1. The permuted block randomization method is used for randomization. Randomization is applied in sequence from subject number 1 using iCReaT, a web-based eCRF. The investigator will perform the surgery according to the results of randomization of the subjects. To minimize possible bias that may arise, randomization is performed by a researcher from the Department of Neurosurgery, and the surgeon is informed of the randomization code immediately before surgery.

This study has limitations in applying the double-blind method. It is inevitable that the investigator knows which procedure was used, and the patient also knows the surgical method due to the incision site after surgery. Therefore, the assessor-blind method, which applies the blinding only to the assessor, is applied, and an assessor is a third person who has not performed the surgery.

Statistical Consideration:

